### (2) Secondary endpoints

Secondary outcomes include: (1) Surgical duration, recorded in minutes from incision to closure; (2) UAS insertion resistance, measured with an IMADA50N push-pull gauge (calibrated monthly for accuracy); (3) Ureteral injury rate, assessed at UAS removal using the Post-Ureteroscopic Lesion Scale (PULS) by two blinded urologists, with a third resolving discrepancies; (4) Stone clearance rate, defined as the proportion of patients stone-free on CT two weeks post-surgery; and (5) AEs, tracked during surgery and for two weeks afterward, including acupuncture-related (e.g., bruising) and surgical (e.g., infection) events. These outcomes capture procedural efficiency, tissue safety, and recovery, with standardized tools and blinded assessments ensuring reliability. Training on PULS grading will be provided to assessors to maintain consistency.

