## **Abstract**

**Introduction:** Retrograde intrarenal surgery (RIRS) is a primary treatment modality for urinary tract stones, and successful placement of the ureteral access sheath (UAS) is a critical procedural step. Preliminary studies have suggested that preoperative electroacupuncture (EA) may improve UAS placement success rates, reduce ureteral injury, and enhance stone clearance outcomes. This trial evaluates the efficacy and safety of EA as an adjunctive therapy in first-stage RIRS.

**Methods and analysis:** This multicenter, randomized, single-blind, sham-controlled trial will enroll 120 adult patients with upper ureteral or renal stones ( $\geq 10$  mm) scheduled for first-stage RIRS. Participants were randomly allocated (1:1) to receive either preoperative EA combined with general anesthesia or sham EA combined with general anesthesia across multiple treatment sessions. The primary outcome is the proportion of patients achieving successful UAS placement during first-stage RIRS. Secondary outcomes included operative time, resistance during UAS insertion, ureteral injury (assessed via the Post-Ureteroscopic Lesion Scale [PULS]), stone clearance rate at 2 weeks postoperatively, and adverse events (AEs) within 2 weeks postoperatively. Data will be analyzed using the intention-to-treat principle.

**Discussion:** This study will be the first randomized controlled trial (RCT) to investigate the efficacy of EA in improving both the success rate and safety of UAS placement during first-stage RIRS. The findings will provide high-quality evidence to support the integration of EA as an adjunctive therapy in clinical practice. Through comprehensive multidimensional assessments, this research will demonstrate the potential for broader application of EA in urolithiasis management. Further rigorously designed clinical trials will be essential to validate and refine this promising therapeutic approach.

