## **Study Protocol**

### **1. Study background**

1. RIRS will serve as a cornerstone intervention for urinary tract calculi, with the successful placement of the UAS during the procedure being a pivotal step.

Identifying strategies to effectively improve UAS deployment success rates will be critical.

Urolithiasis will remain a prevalent condition in urology, with recent epidemiological surveys projecting a prevalence rate of 1.61%–20.45% in China, an

aggregate rate of 7.54%, and a rising trend [1]. Minimally invasive endoscopic procedures, including rigid ureteroscopy, flexible ureteroscopy, percutaneous nephrolithotomy, and laparoscopic lithotomy, will be required for many patients [2]. Advancements in technology will establish RIRS as a primary modality for urinary stone management. During RIRS, the placement of the UAS will constitute the initial and crucial procedural step [3]. Successful UAS insertion will depend on mitigating resistance caused by ureteral spasm secondary to stone obstruction and inherent ureteral strictures. Excessive force during sheath placement will risk ureteral injury, including perforation, avulsion, or rupture [3]. However, quantitative thresholds defining "excessive force" will remain undefined. While studies will identify risk factors influencing insertion resistance [4–6], effective protocols to reduce resistance and ureteral trauma during first-stage RIRS will not yet be established. Preoperative alpha-blocker therapy administered one week prior to surgery will enhance UAS placement success rates in first-stage RIRS. However, patients presenting with acute pain may find a one-week medication delay incompatible with their urgent need for symptom relief. Thus, developing approaches to expedite surgery while optimizing UAS insertion success will be imperative.

2.EA—demonstrating potential to relax ureteral smooth muscle effectively.

However, whether EA can enhance the success rate of UAS placement during first-stage RIRS will remain unexplored.

Clinically, acupuncture will exhibit efficacy across diverse conditions: alleviating pain (e.g., headaches, musculoskeletal pain, arthritis), treating neurological disorders (e.g., facial paralysis, post-stroke sequelae, insomnia), and modulating gastrointestinal function (e.g., gastralgia, diarrhea, constipation). It will also address gynecological, andrological, and otorhinolaryngological ailments. Compared to modern medicine,

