### 2.3 Local Tissue Regulatory Mechanisms

2.3.1 Enhanced Blood Circulation: EA promotes local blood circulation, improving oxygen and nutrient delivery while reducing the accumulation of metabolic byproducts. This mitigates tissue edema and inflammation, alleviating ureteral smooth muscle spasm.

2.3.2 Muscle Tone Regulation: EA may directly regulate ureteral smooth muscle tone. Stimulation of specific acupoints induces alternating contraction and relaxation of local muscles, modulating ureteral tension through neural reflexes, humoral regulation, or direct mechanical stimulation.

The mechanisms underlying EA-induced ureteral smooth muscle relaxation are multifaceted, involving neuroendocrine and local tissue regulation. While research into these mechanisms remains ongoing, EA—a fusion of traditional and modern therapeutic approaches—has demonstrated clinical efficacy in relieving ureteral spasms and enhancing urinary drainage.

3. Preliminary experiments conducted by our research team have demonstrated that EA significantly enhances the success rate of UAS placement, reduces ureteral injury, and improves stone clearance rates during first-stage RIRS, warranting further investigation.

Preliminary investigations by our research team have demonstrated that EA significantly enhances the success rate of UAS placement, mitigates intraoperative ureteral injury, and improves stone clearance rates during first-stage RIRS. The observed efficacy may be attributed to EA's multifaceted mechanisms. First, optimizing UAS placement is critical to procedural success, as it serves as the foundational step in RIRS. By modulating ureteral smooth muscle tone, EA likely induces relaxation, thereby facilitating sheath insertion, reducing operative time and technical challenges, and enhancing overall procedural safety. Second, EA's ability to minimize ureteral trauma addresses a major intraoperative risk. Ureteral injury during RIRS may lead to postoperative complications such as strictures or urinary leakage. EA appears to exert protective effects by improving local microcirculation and attenuating inflammatory responses, thereby preserving tissue integrity. Finally, improved stone clearance is vital for patient recovery, as residual calculi increase recurrence risks and impose physical and economic burdens. EA may enhance intraoperative stone expulsion by promoting ureteral peristalsis and optimizing urinary drainage.

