### **4.Sample size estimation**

Based on preliminary trial results demonstrating a 90% success rate of UAS placement in the EA group compared to 75% in the sham EA group, this study adopts a conservative estimate that EA will yield at least a 15% superiority over sham EA for sample size calculation. With a two-sided significance level of 0.05, a 1:1 allocation ratio between groups, and 0.28 confidence interval width, a total of 110 participants (55 in the EA group and 55 in the sham EA group) are required to detect this superiority. Accounting for a potential 10% attrition rate, the adjusted sample size is 120 patients.

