### **5.Interventions**

#### **5.1 Surgical and Anesthetic Method**

Both the experimental and control groups underwent flexible ureteroscopy with ureteral stent placement in the operating room. Following lithotomy positioning,

participants received either EA or sham EA 10 minutes prior to general anesthesia induction, with stimulation maintained until procedure completion.

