## 6.Clinical observation index

### (1) Primary endpoint

The primary endpoint is the proportion of patients who achieved successful UAS placement and completed the first-stage RIRS without major intraoperative complications.

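### Surgical duration is timed between two events that do not occur in retrograde ureteroscopy, so the endpoint cannot be recorded as defined

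*Protocol*

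**What the plan says.** Section 6 of the protocol, under Secondary endpoints, lists as item 1 "Surgical duration, recorded in minutes from incision to closure". The Abstract names the same outcome without start or stop: "Secondary outcomes included operative time, resistance during UAS insertion".

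Section 5.1 describes the operation: "Both the experimental and control groups underwent flexible ureteroscopy with ureteral stent placement in the operating room". The Study background places flexible ureteroscopy among endoscopic procedures and says of the access sheath (UAS) that "the placement of the UAS will constitute the initial and crucial procedural step". The same section, item 3, expects EA to act by "facilitating sheath insertion, reducing operative time and technical challenges".

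Two further statements bear on how a duration would be read. The primary endpoint counts patients who "achieved successful UAS placement and completed the first-stage RIRS without major intraoperative complications", so non-completion is foreseen. The sample size section rests on preliminary results "demonstrating a 90% success rate of UAS placement in the EA group compared to 75% in the sham EA group".

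**The concern.** A time endpoint needs a start and a stop that staff in theatre can see. The two named here belong to open surgery. Retrograde flexible ureteroscopy reaches the stone through the urinary tract, and the protocol mentions no skin incision or wound closure anywhere. In a multicentre trial, each centre would have to substitute its own events. A time that was not stamped cannot be recovered afterwards, so this cannot be left to the analysis.

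A second, smaller question is interpretation. Sheath placement comes first in the operation, and the planning figures put failure at different rates in the two arms. If failed cases take a different time from completed ones, mean duration mixes success with speed. The protocol expects EA to shorten the operation, so a difference in completion could be misread as a difference in speed.

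**Working it through.** **1. Timing events against the operation.**

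- Start named in section 6: an incision. Sections 5.1 to 5.3 describe positioning, needling, anaesthesia and ureteroscopy with stent placement, but no incision.
- Stop named in section 6: closure. No section describes one.
- Alternatives elsewhere: none. The Abstract gives only the name of the outcome.

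Section 5.1 alone offers several starts a centre might choose: lithotomy positioning, start of (sham) stimulation, or induction. Insertion of the first endoscope is another. Stimulation begins 10 minutes before induction, so two centres choosing those two starts would differ by 10 minutes for identical operations. Adjusting for centre would remove a constant offset from the comparison of arms. It would not give the centres a common quantity, and it would not help where the clock varies within a centre.

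**2. Planning rates.** The protocol gives no mean, standard deviation or target difference for duration, so it has no duration figure to reproduce. The success rates can be checked against the stated sample size. With a Wald confidence interval of total width 0.28:

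n per arm = [0.90 × 0.10 + 0.75 × 0.25] × (1.96 / 0.14)² = 0.2775 × 196 = 54.4, rounded up to 55.

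This matches the stated 55 per arm, so 90% and 75% are the rates the plan uses. Their complements are 10% and 25% sheath failure.

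**3. Effect of differing completion on mean duration.** Let Tc be the mean time of completed cases and Ta that of non-completed cases, with no EA effect on either. Suppose that every sheath failure is a non-completed case and that no other case is.

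- Mean (EA) = 0.90 Tc + 0.10 Ta
- Mean (sham) = 0.75 Tc + 0.25 Ta
- EA minus sham = 0.15 × (Tc − Ta)

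The documents give no durations. All times below are assumptions.

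| Tc (min) | Ta (min) | EA mean | Sham mean | EA − sham |
|---|---|---|---|---|
| 60 | 30 | 57.0 | 52.5 | +4.5 |
| 60 | 20 | 56.0 | 50.0 | +6.0 |
| 90 | 20 | 83.0 | 72.5 | +10.5 |
| 90 | 15 | 82.5 | 71.25 | +11.25 |
| 60 | 60 | 60.0 | 60.0 | 0 |
| 60 | 80 | 62.0 | 65.0 | −3.0 |

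If only half of the failures in each arm go uncompleted and the rest take the usual time, the shift halves. At Tc = 60 and Ta = 20 to 30 it falls from 4.5–6 to 2.25–3 minutes.

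**The case against.** The strongest reply is that the phrase is a stock description of operating time which any surgeon would read as start to end of the procedure, and that CRF instructions, not at hand, may settle it. That may be so, but the protocol text is what is fixed, and it names events this operation does not have. Start and end are exactly what has to be specified. One detail does count against a careless version of the argument: the background's list of endoscopic procedures also includes percutaneous and laparoscopic ones, so the word endoscopic alone does not rule out an incision. It is the retrograde ureteroscopic route in section 5.1 that does.

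A reader might go further and infer that abandoned cases will shorten the sham mean, so that the endpoint is biased against EA. The documents do not support this. No section says that a failed sheath placement ends the operation. The primary endpoint lists placement and completion as separate conditions, and the 90% and 75% are placement rates, not completion rates. No durations are given, and the last two rows of the table show that the shift can be zero or reversed. How non-completed cases enter the analysis is also commonly left to a SAP, which is not shown here.

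A reader might likewise want to replace the outcome with sheath insertion time, rank failed attempts worst, or demote operative time to description. These are preferences. Insertion resistance is already measured, and ranking failures worst would partly count the primary endpoint twice.

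**Conclusion.** The definition of surgical duration is wrong as written. Its start and stop do not exist in the operation described, and nothing else in the protocol supplies them. This rests on the text alone and needs no assumed figure.

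The effect of differing completion is a conditional risk. It equals 0.15 × (Tc − Ta) if the planning rates hold and every sheath failure goes uncompleted, and less if only some do. With assumed times of 60–90 minutes for completed and 15–30 minutes for non-completed cases, it is +4.5 to +11.25 minutes against EA. It is zero at equal times and −3 minutes at 80 against 60. Neither sign nor size can be determined from the documents.

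The reach is limited. This is one of five secondary outcomes, and neither the primary endpoint nor the sample size depends on it. It is still worth correcting, because unstamped times cannot be restored later.

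**What to change.** In section 6, replace the start and stop with observable endoscopic events that apply to every patient and every centre, for example first endoscope insertion to removal of the last instrument. Use the same wording in the CRF.

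Add a supporting table of duration by arm and by status (sheath placed or not, RIRS completed or not). It should be read descriptively, because status arises after randomisation and a comparison within completers is not a randomised one. Its purpose is to keep a difference in completion from being read as a difference in speed. New timing events alone would not achieve that.

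The cost is protocol and CRF wording and one extra table. Sample size and primary analysis are unchanged.

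### Ureteral injury has one grading point, UAS removal, so patients whose sheath could not be placed (planned 10% of EA, 25% of sham) have no stated PULS grade

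*Protocol*

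**What the plan says.** Protocol section 6, Secondary endpoints, item 3, defines the outcome as "Ureteral injury rate, assessed at UAS removal using the Post-Ureteroscopic Lesion Scale (PULS) by two blinded urologists", with a third urologist settling disagreements. That is the only time point given. The item states no denominator and no rule for a patient in whom the sheath was not placed.

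Three other places bear on it:

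- **Section 4** takes its planning rates from "preliminary trial results demonstrating a 90% success rate of UAS placement in the EA group compared to 75% in the sham EA group".
- **Section 1** names the insertion attempt as a source of harm: "Excessive force during sheath placement will risk ureteral injury, including perforation, avulsion, or rupture". It also presents less ureteral injury as a benefit of EA and lists injury among the key endpoints.
- **The Abstract** states: "Data will be analyzed using the intention-to-treat principle".

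Safety is also followed through item 5 of the same list: "AEs, tracked during surgery and for two weeks afterward, including acupuncture-related (e.g., bruising) and surgical (e.g., infection) events". This is not limited to patients whose sheath was placed.

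**The concern.** A sheath that was never placed is, on the plain reading, never removed, so the grading trigger does not occur. Whether a patient is graded then depends on placement success, which is the primary outcome in the Abstract and the first component of the primary endpoint in section 6. The trial expects that to differ by arm. The graded EA and sham groups would be selected differently after randomisation, and the EA group would include difficult ureters that would have dropped out of the sham group.

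At stake is whether the trial can test its own claim that EA reduces ureteral injury. The lesion has to be seen and graded during surgery. A statistical analysis plan can choose a denominator or an imputation rule, but it cannot recover a grade that nobody assigned.

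**Working it through.** **1. Inputs from section 4.** Success is 90% (EA) and 75% (sham). The precision basis is "With a two-sided significance level of 0.05, a 1:1 allocation ratio between groups, and 0.28 confidence interval width". The size is "a total of 110 participants (55 in the EA group and 55 in the sham EA group) are required", and then "Accounting for a potential 10% attrition rate, the adjusted sample size is 120 patients".

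**2. Do these rates drive the plan?** For a Wald 95% interval of full width 0.28:

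n per arm = [0.90×0.10 + 0.75×0.25] × (2×1.96/0.28)² = 0.2775 × 196 = 54.4, rounded up to 55.

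The stated 55 per arm is reproduced, so 90% and 75% are the working rates. Attrition gives 110/0.9 = 122.2, or 123, close to the stated 120. The sample size is not disputed here.

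**3. Expected ungraded patients** = n × (1 − success rate).

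| Per arm | EA ungraded | Sham ungraded | EA graded | Sham graded |
|---|---|---|---|---|
| 60 | 6 | 15 | 54 | 45 |
| 55 | 5.5 | 13.75 | 49.5 | 41.25 |

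**4. Effect on the comparison.** The protocol gives no injury rates, so every risk below is an assumption.

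*Range.* Let injury be 20% in placed patients of both arms, and let the risk after a failed attempt run from 20% to 80%.

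- All randomised, at 20%: 20% vs 20%, difference 0.
- All randomised, at 80%: EA 0.90×0.20 + 0.10×0.80 = 26%; sham 0.75×0.20 + 0.25×0.80 = 35%; difference −9 points.
- Graded patients only: the difference is 0 throughout.
- Ungraded patients counted as uninjured: 0.90×0.20 = 18% vs 0.75×0.20 = 15%, which favours sham by 3 points as an artefact.

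The direction is not fixed. With 30% in placed and 20% in failed patients, the all-randomised rates are 29% vs 27.5%, while the graded difference is still 0.

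*Can the sign change?* Split patients into 75% placed in either arm (risk r1), 15% placed only with EA (risk r2 if placed) and 10% never placed. Let rf be the risk after a failed attempt, and let EA act only through placement. Then, EA minus sham:

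- graded only: (0.75·r1 + 0.15·r2)/0.90 − r1 = (r2 − r1)/6
- all randomised: 0.15 × (r2 − rf)

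The signs are opposite whenever r1 < r2 < rf. With 15%, 30% and 40%:

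- all randomised: 0.1125 + 0.045 + 0.04 = 19.75% vs 0.1125 + 0.10 = 21.25% (−1.5 points)
- graded only: 0.1575/0.90 = 17.5% vs 15.0% (+2.5 points)

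Now let EA also lower r1 from 15% to 10%, leaving the rest unchanged:

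- all randomised: 0.075 + 0.045 + 0.04 = 16.0% vs 21.25% (−5.25 points)
- graded only: 0.12/0.90 = 13.3% vs 15.0% (−1.7 points)

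The sign no longer changes, but the benefit is understated.

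**5. Precision.** At 60 per arm and about 20% injury, the standard error of the difference is √[(0.1975×0.8025 + 0.2125×0.7875)/60] = 7.4 points, a 95% half-width of about 14 points. The shifts in these illustrations are smaller than that.

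**6. Could the analysis bound the problem without grades?** Best-case and worst-case grades move the difference across 10% + 25% = 35 points, whatever the graded rates are. With 20% injury among the graded (10.8 of 54 and 9 of 45), the extremes are 16.8/60 − 9/60 = +13 points and 10.8/60 − 24/60 = −22 points. Bounds are useful only if few patients are left ungraded.

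**The case against.** The protocol does not say that failed placements are excluded. It names a time and is silent on the rest, and withdrawal of a partly advanced sheath could be read as removal. This stands as a limit: non-grading is inferred from the single stated trigger. It does not remove the need for a change, because centres that read the trigger differently would grade differently.

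A reader might infer that injuries from failed insertions go uncounted. The documents do not support that. Adverse events are tracked during surgery in all patients, and perforation, avulsion or rupture would fall there naturally. What is lost is the blinded PULS grade, mainly for lower-grade lesions. The section 6 primary endpoint also refers to major intraoperative complications, but a patient with failed placement has already failed it, so it adds nothing for that patient.

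A reader might also infer that the trial would falsely show EA to reduce injury, or that the sign will reverse. Neither follows. If failed attempts are the more injurious, omitting them works against EA. The reversal rests on assumed risks and on EA having no effect in easily placed ureters, whereas section 1 hypothesises a direct protective effect.

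Denominators and missing-data rules for a secondary endpoint can properly sit in a statistical analysis plan, and the intention-to-treat sentence is general. That is fair. The point here is the assessment time, which the protocol itself fixes.

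Finally, one might extend the criticism to insertion resistance. Item 2 does not limit that measurement to successful placements, so no defect is shown there.

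**Conclusion.** The point holds as a gap in the assessment trigger that is unequal by arm. Following the text as written, about 10% of EA and 25% of sham patients (6 and 15 of 60) would have no PULS grade. The injury comparison would then be conditioned on placement success and would not be an intention-to-treat comparison.

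This rests on two things: the plain reading of removal, and planning rates that may not be the observed ones. The likely direction, against EA, further assumes that failed attempts carry more injury, which section 1 makes plausible but does not quantify. The size of the bias cannot be derived from the documents. In the illustrations it runs from nothing to 9 points, and a sign change is possible but not established. The wording should be changed before more patients are treated, because missing grades cannot be recovered afterwards.

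**What to change.** In section 6, Secondary endpoints, item 3, change the trigger to: PULS is graded at the last endoscopic view of the ureter obtained during the first-stage procedure after any UAS attempt, that is, at UAS removal, or at the end of the procedure if the sheath was not placed. State that the denominator is all randomised patients.

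The protocol does not describe what view of the ureter is available after a failed placement. Where none exists, require no extra procedure, record the patient as ungraded, report the count by arm, and give the injury difference under best-case and worst-case grades.

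The cost is a wording change in the protocol and case report form and a few more gradings by the same raters. Some patients will remain ungraded. The insertion-resistance item needs no change on this account.

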## 5.2 EA Protocol for the Experimental Group

In addition to standard general anesthesia, EA was administered 10 minutes preoperatively and sustained intraoperatively. Sterile acupuncture needles (Hwato brand, 0.25 mm × 40 mm) were inserted at Sanyinjiao (SP6), Zhaohai (KI6), and Taixi (KI3). After lifting, thrusting, and rotating the needles for 30 seconds, an electronic stimulator (SDZ-II model, Hwato brand) was connected, delivering continuous wave at 50 Hz with current intensity adjusted between 1–5 mA (maximal tolerable level without pain). Licensed acupuncturists with ≥5 years of experience performed all interventions following standardized training on acupoint localization and needling techniques. Should any acupuncture-related adverse events occur, the acupuncture needles will be immediately removed. The specific acupoint localization protocols are as follows:

| Acupoint
(international
code) | Location                                                                                                                    | Angle and Depth                                                        |
|-------------------------------------|-----------------------------------------------------------------------------------------------------------------------------|------------------------------------------------------------------------|
| Sanyinjiao(SP6)                     | The medial side of the lower leg, 3 cun above the tip of the medial malleolus, posterior to the medial border of the tibia. | Insert the needle perpendicularly to the skin to a depth of 1-1.5 cun. |
| Zhaohai (KI6)                       | 1 finger-width medial to the ankle joint.                                                                                   | Insert the needle perpendicularly to the skin to a depth of 1.5-2 cun. |
| Taixi (KI3)                         | 2 finger-width medial to the ankle joint.                                                                                   | Insert the needle perpendicularly to the skin to a depth of 1-1.5 cun. |

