## 5.3 Sham EA Protocol for the Control Group

Participants in the control group will receive sham acupuncture following the same procedural timeline as the experimental group. Needles will be inserted 3 mm lateral to the verum acupoints in non-meridian, non-acupoint regions using superficial needling (1–4 mm penetration depth) without needle manipulation (lifting, thrusting, or

rotating) . Following sham needling, the needles will be connected to a deactivated electroacupuncture device with internally short-circuited wiring to prevent current output. Should any acupuncture-related adverse events occur, the needles will be immediately removed. Sham acupuncture will be performed by licensed acupuncturists with  $\geq 5$  years of experience, who will undergo standardized training in sham acupoint localization and needling techniques prior to trial commencement.

The comparative characteristics of the experimental and control groups, including their shared features and key distinctions, are summarized in the table below:

| Program                                | Experimental Group                              | Control Group                                           |
|----------------------------------------|-------------------------------------------------|---------------------------------------------------------|
| Common Points                          |                                                 |                                                         |
| Stimulated Point Area                  |                                                 | Leg                                                     |
| Number of Acupoints/Non-Acupoints      |                                                 | 6                                                       |
| Number of Needles                      |                                                 | 6                                                       |
| Specifications of Needling Instruments | Length: 4 mm, Diameter: 0.25 mm                 |                                                         |
| Difference                             |                                                 |                                                         |
| Types of Stimulated Points             | Acupoint                                        | Non-Acupoint                                            |

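### The abstract and section 6 give different adverse-event windows, and neither starts at first needle insertion, so acupuncture reactions that resolve before surgery can be missed

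*Protocol*

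**What the plan says.** The AE outcome is defined twice. Section 6 (2), item 5, has "AEs, tracked during surgery and for two weeks afterward, including acupuncture-related (e.g., bruising) and surgical (e.g., infection) events". The Methods paragraph of the abstract has "adverse events (AEs) within 2 weeks postoperatively".

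Exposure is described in section 5. Section 5.1 states that "participants received either EA or sham EA 10 minutes prior to general anesthesia induction, with stimulation maintained until procedure completion". Section 5.2 says of the experimental arm that "EA was administered 10 minutes preoperatively and sustained intraoperatively", with "current intensity adjusted between 1–5 mA (maximal tolerable level without pain". Section 5.3 puts the control arm on the same clock: "Participants in the control group will receive sham acupuncture following the same procedural timeline as the experimental group". The sham device delivers no current.

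Section 5.2 foresees reactions to the needling: "Should any acupuncture-related adverse events occur, the acupuncture needles will be immediately removed". Section 5.3 has a matching sentence for sham. Neither sentence says whether the event enters the AE outcome.

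**The concern.** A safety window should open when exposure opens. Here exposure begins before induction, while the stated windows open at surgery (section 6) or after it (abstract).

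The uncovered minutes matter more than their length suggests. They are the only part of the exposure in which the patient can report pain, faintness or intolerance of the stimulation. After induction such complaints cannot be made.

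Any loss may also differ by arm. EA involves needling to roughly 10–30 mm, 30 seconds of manipulation and live current. Sham involves 1–4 mm, no manipulation and no current. Transient reactions that go uncounted could therefore plausibly come more often from the EA arm. Safety of EA is one of the trial's stated aims.

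The disagreement between the two definitions is a separate problem. A site or analyst working from the abstract would leave out intraoperative events that section 6 counts.

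**Working it through.** The plan has no figure to reproduce and the point depends on no formula, so the check sets the exposure period against the two AE windows.

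**Inputs**
- Exposure starts 10 minutes before induction (section 5.1), or 10 minutes before the operation (section 5.2). Sham follows the same timeline (section 5.3).
- Exposure ends when the procedure is complete (section 5.1).
- AE window A (abstract): the 2 weeks after surgery.
- AE window B (section 6): surgery plus the two weeks after it.

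**Coverage by phase, read literally**

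| Phase | Under EA or sham? | Window A (abstract) | Window B (section 6) |
|---|---|---|---|
| Needling, about 10 minutes up to induction | Yes | Not covered | Not covered |
| Induction to start of surgery | Yes | Not covered | Not covered |
| Surgery | Yes | Not covered | Covered |
| Two weeks after surgery | No | Covered | Covered |

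**Coverage by type of event**
1. Begins and resolves before surgery (faintness, pain on needling, intolerance of the current): outside both windows.
2. Begins during needling and persists (bruising, which is the protocol's own example): inside B, and inside A if still present after surgery.
3. Arises and resolves during surgery: inside B, outside A.
4. Arises after surgery: inside both.

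Types 1 and 3 are the ones affected. Type 3 is lost only under the abstract's wording. Type 1 is lost under both.

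**Does surgery, in section 6, include the needling period?** Three places suggest that it does not. Section 5.2 separates a preoperative phase of EA from an intraoperative one. The abstract calls the intervention preoperative. Item 1 of the same list in section 6 times the operation from the first cut to the closing of the wound, and needling precedes that. One place points the other way: section 5.1 puts the needling in the operating room, after positioning, under a heading on surgical and anaesthetic method. The literal reading is therefore the more natural one, but the text does not settle it.

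**Is the patient awake in the uncovered period?** The protocol does not use the word. The inference is sound: needling precedes induction, the current is set to what the patient tolerates, and the table in section 5.3 lists a deqi sensation for EA.

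**The case against.** The strongest reply is that section 6 expressly includes acupuncture-related events and that stimulation runs through the procedure, so most of the exposure and all of the follow-up lie inside the fuller definition. That stands. A reader might infer from the late start that treatment-emergent acupuncture events as a class are outside the safety endpoint, or that none of the events arising while the patient is awake would be captured. The documents do not support either inference. An event that starts at needling and persists is still present when the section 6 window opens.

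A second reply is that needling in the operating room is loosely part of surgery, so nothing is excluded. This stands only in part. It shows an ambiguity, but section 5.2's own split into two phases works against it, and sites could record the same event differently.

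A third is that the abstract is only a summary and section 6 would prevail. That is likely, and it makes the abstract's omission of intraoperative events the lesser problem. It does not help with the start of the window, which section 6 also leaves after the start of exposure.

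A fourth is that the direction of any bias is conjecture. Both arms receive six needles, and faintness or needling pain can occur in either; only intolerance of current is specific to EA. This is fair. A difference between arms is plausible from the contrast in depth, manipulation and current, but nothing in the protocol quantifies it.

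Finally, nothing says that a reaction leading to needle removal goes unrecorded. True, but nothing says that it is recorded in the endpoint, and the stated window would leave it out.

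**Conclusion.** The point holds in a limited form. The protocol states two different AE windows for one outcome, and neither begins at first needle insertion. Read literally, acupuncture reactions that begin and resolve before surgery fall outside the endpoint, even where they led to needle removal. Intraoperative events are inside section 6 but outside the abstract.

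The gap is about 10 minutes of needling plus any interval between induction and the start of surgery. The number of events at stake cannot be estimated, because the documents give no rate of such reactions. A reader might go on to conclude that EA will look safer than it is; the text supports only that uncounted transient reactions could plausibly be more frequent in the EA arm.

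The conclusion rests on reading surgery in section 6 as not including the earlier needling, and on the inference that the patient is awake before induction. The primary endpoint, the sample size and the efficacy comparison are unaffected. The change should be made because the plan states a window that does not match the exposure, and correcting it is nearly free.

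**What to change.** Use one sentence in both the abstract and section 6 (2), item 5: *AEs are recorded from first needle insertion (EA or sham) until 2 weeks after surgery.* Add to section 6 that any acupuncture-related event leading to needle removal, in either arm, counts as an AE in this endpoint. This concerns recording only and leaves the removal provisions in sections 5.2 and 5.3 untouched.

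Tabulating events as pre-induction, intraoperative and postoperative would make the table easier to read, but it is optional and can be left to the analysis plan.

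The cost is a wording change in two places and one added sentence, with the recording form and site instructions matched to the same start point. No extra visits or patients are needed.
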